
#### Medical record audit

Demographic and clinical data collected from the patient medical record will include: age, gender, stage of disease; length of time since diagnosis; treatment received in past; ECOG performance status, medications and chemotherapy treatment regimen. Usage of hospital resources will be undertaken via medical record audit to assess emergency room presentations, unplanned hospital admissions, total bed days of care. Use of nursing time, allied health services, clinical investigations/procedures and other related staff time and resource use by patients in both conditions will be recorded. Changes in chemotherapy treatment dose including dose reductions, and treatment delays will also be recorded.

#### Structured costs interview

Use of other health services (and patient-related costs) not recorded in the primary patient medical record, will be assessed through the use of the Patient Health Services and Costs Interview. This interview is conducted with the patient by the DM to identify which health- related services were utilised and any medications prescribed/used in the previous cycle in order to assign costs.

#### External hospital data

In the case where DMs identify that a patient has been treated and/or admitted to a hospital which is *not* the primary treating hospital from the medical record audit or costs interview then a letter to this external treating hospital will be sent requesting basic details.

#### PRISMS electronic log data

Data from the PRISMS log files will be utilised to assess patient compliance with daily symptom reporting and reported use of self care activities. Log data will also be used to assess nursing compliance with the system including: timely response to alerts; documentation of actions taken in response to alerts and completion of checklists documenting scheduled interventions.

### The PRISMS intervention

The PRISMS intervention is guided by 5 principles which are linked to improved patient outcomes including: 1) *promotion of patient involvement and engagement* [13, 61]; 2) *tailoring to specific need* [62]; 3) *emphasising evidence based self-management* [13, 63–67]; 4) *involvement of significant others* [68] *and*; 5) *preparing patients for treatment and potentially threatening medical procedures* [13, 69–71].

The PRISMS intervention will include two synergistically operating parts: 1) *a mobile phone-based remote monitoring system* with built in patient self-care advice and clinician alerting algorithms [43]; and 2) *a structured nursing support intervention relating* to: patient use of the remote monitoring system; patient coaching in self-care strategies and *ongoing* access to 24-hour nursing support/clinical interventions, triggered by real-time system alerts.

#### The mobile phone enabled remote monitoring system

This system is based on the prototype previously developed and piloted [43] and based on the ASyMS system developed by [name] et al. [36]. Patients are provided with a 7″ Android tablet which has the remote monitoring software application installed. Patients are trained in the use of the remote monitoring system by nurses. The Android application prompts patients twice daily to complete a side-effect assessment questionnaire by following instructions on the touch screen (Fig. 2). Patients can also complete questionnaires at anytime they feel unwell. The questions about common chemotherapy related side-effects are based on the Chemotherapy Symptom Assessment Scale [72] which measures both severity (mild, moderate, severe) and distress (not at all, a little, quite a bit, very much) caused by symptoms. Symptom severity *descriptors* were adapted from the Common Toxicity criteria for Adverse Events (CTCAE V4.0) [73] for consistency in interpretation between patients and clinical grading of symptoms by clinicians. Side-effects monitored include: rigors, bleeding, nausea, vomiting, diarrhoea, mucositis, fatigue, constipation and peripheral neuropathy. Patients are also prompted to rate their ability to complete daily living activities [73] and to input additional parameters such as body temperature, food intake and fluid intake into the system. Once weekly, patients also answer questions about levels of anxiety, depression and psychological distress as well as their use of self-care behaviours to alleviate side-effects. At the completion of each patient questionnaire the Android application automatically uploads and encrypts all patient questionnaire data via General Packet Radio Services to a secure study server.

**Fig. 2 Fig2:**
[figure not shown]
Screenshots from the Patient Remote Intervention and Symptom Management System (PRISMS) patient remote monitoring application illustrating: **a** Temperature input. **b** Assessment of vomiting

The report of any side-effects by patients completing the questionnaire triggers the provision of tailored evidence-based self-care advice to the patient (Fig. 3). The self-care advice was developed from a systematic review of the literature [74] and in consultation with haematology clinicians and patient advisors, and tested in our previous pilot study [43]. The self-care advice consists of simple instructions to self-manage side-effects. The patient tablet application also contains a graphing function for patients to view their side-effects profiles over time and an extensive library of written, audio and video information resources (Fig. 3).

**Fig. 3 Fig3:**
[figure not shown]
Screenshots from the Patient Remote Intervention and Symptom Management System (PRISMS) patient remote monitoring device showing: **a** The main menu. **b** A graph illustrating the severity and bother due to nausea. **c** An excerpt of self-care information about constipation

##### Clinician alerts

The server software which receives patient data contains in-built decision support algorithms which act to trigger Email alerts to a dedicated mobile phone held by nurses. Alerts are divided into two categories: red – for life-threatening or urgent issues (eg fever) which must be addressed within 15 minutes and; amber – for moderate/non-life-threatening issues which should be addressed within 8 hours. Alerts are based on those developed from a review of the literature, extensive clinician consultation and then subsequently piloted and refined in a previous pilot study [42]. Alerts are based on either the severity and/or distress relating to reported side-effects. In addition, patients who have not completed side-effect questionnaires for > 24 hours will also generate an alert to nurses known as a ‘missing alert’ which also requires follow-up within 8 hours.

Upon receipt of alerts, intervention nurses will access a secure website to view the latest patient questionnaire data. A history of patient symptoms across cycles is provided in both tabular and graphical formats to quickly orient the nurses to the patient’s situation (Figs. 4 and 5). Trained nurses contact the patient by phone to undertake further assessment and management. Evidence-based triage and assessment algorithms are also provided on the secure website alongside evidence-based self-care information to direct nursing care. Intervention nurses record all actions in a series of open fields and drop down boxes on the secure website. Monitoring of patients (via the SMS alerting system) occurs 24 hours/day.

**Fig. 4 Fig4:**
[figure not shown]
Screenshot from the Patient Remote Intervention and Symptom Management System (PRISMS) clinician website illustrating a graphical summary of a patient temperature profile with graph selector menu

**Fig. 5 Fig5:**
[figure not shown]
Screenshot from the Patient Remote Intervention and Symptom Management System (PRISMS) clinician website illustrating history of individual patient alerts and side-effects reported

#### Structured nursing support enabling self-management

The structured nursing support component of this intervention will include 6 scheduled face-to-face or phone intervention sessions (Fig. 6).

**Fig. 6 Fig6:**
[figure not shown]
Summary flow diagram of the Patient Remote Intervention and Symptom Management System (PRISM) intervention (Abbreviations: C1D1, Day 1 of chemotherapy treatment cycle 1; C2D1, Day 1 of chemotherapy treatment cycle 2; C3D1, Day 1 of chemotherapy treatment cycle 3; C4D1, Day  1 of chemotherapy treatment cycle 4)

*Intervention Session 1:* this 50-minute face-to-face session occurs directly following pre-chemotherapy education and incorporates 4 components: i) training in the use of the mobile phone remote monitoring system; ii) eliciting and responding to patient’s key concerns; iii) provision of evidence-based side-effect management strategies and; iv) coaching in self-care advice for most frequent side-effects. Coaching involves reinforcing the importance of patients communicating about their side-effects with the treatment team; identifying potential barriers to self-care, reinforcing the benefits of self-care interventions, assisting the patient to develop plans to overcome barriers to self-care action and where appropriate encouraging the involvement of the patient’s family in self-management [60–62].*Intervention Sessions 2–6* : Intervention Sessions 2 (15-minute face-to-face) and 3–6 (15-minute via telephone) focus on answering additional patient questions about treatment or use of the system, coaching in use of self-care and utilisation of the full functionality of the PRISMS tablet computer application (Fig. 6).

### Quality control

#### Training intervention nurses

At each site specialist cancer nurses will be trained to provide scheduled patient interventions during business hours and to respond to real-time patient generated system alerts. Training will take place in 2 sessions of 4 hours and consists of: a project overview; developing familiarity and skills in the use of the remote monitoring/management system and responding to system alerts; communication skills training for in eliciting and responding to emotional cues; coaching in self-care strategies and; role-play scenarios with simulated patients. A detailed intervention manual containing all aspects of the training as well as evidence-based self-care algorithms will also be provided to all intervention nurses.

#### After hours nurses

After hours nurses will be trained in how to respond to real-time patient generated system alerts using the website. A short manual containing instructions on how to respond to alerts and use the website will be provided.

#### Data manager training

DMs with experience in participant recruitment and coordinating research projects will be trained to identify eligible patients, liaise with hospital staff and intervention nurses, approach patients, randomise consenting patients, administer pen-and-paper outcome measures and interviews at all data collection time points, manage participant databases, and report data back to the project team.

#### Quality assurance of the intervention

All scheduled face-to-face and phone interventions will be digitally recorded for assessment of content and adherence to the intervention manual. Intervention nurses will also be required to record all interactions and interventions within the PRISMS website from drop down menus/open text boxes. Completeness of intervention delivery can then be assessed for adherence to the intervention manual with data from both the recorded conversations and data entered into the website. The time taken for intervention nurses to respond to red/amber alerts will be recorded automatically by the website to ensure that alerts are responded to within designated time frames. All nurses involved in the study, will have access to evidence-based algorithms/self-care strategies for managing patient side-effects on the system. Nursing responses to real-time patient alerts documented on the system will be assessed for compliance with triage algorithms provided.

Patient adherence to daily completion of side-effect questionnaires with the Android application will be assessed for timeliness and patient *use* of the prescribed self-care information provided by the Android application will also be monitored with a weekly self-report questionnaire.

#### Diffusion of the intervention

Diffusion of an intervention relates to how a novel idea or practice spreads through a population – for example the adoption of a new behaviour. In the case of an intervention study such as PRISMS, it is possible that nurses trained to deliver the PRISMS intervention may discuss novel practices with nurses delivering Usual Care; thus changing Usual Care and diluting the potential overall intervention effect. In a previous study of a pre-CTx education intervention [13] we successfully trained a subgroup of Day Chemotherapy Unit nurses for intervention delivery. A random analysis of recordings from both control and intervention group education sessions subsequently showed *no evidence of diffusion over time*. In this study diffusion will be minimised by: 1) instructing intervention nurses about the effects of diffusion/impact on study outcomes; 2) intervention nurses not treating control group patients and; 3) control group patients not using the remote monitoring system thereby removing the alerts which structure a large component of the intervention.

Nurses who monitor real-time alerts after hours will not be able to avoid potentially providing care to control group patients who may ring the switchboard for information/clinical advice. However, when these nurses manage control group patients they will not have ready access to the evidence-based triage algorithms/self-care information located on the system website or data from side-effect history profiles available to intervention patients.

### Standard of care

#### Control group

Patients allocated to the control group will receive the following resources from the DM following randomisation: an evidence-based patient preparation for chemotherapy DVD [13]; a standard booklet ‘*Introduction to Chemotherapy*’; and standard drug information sheets. Control group patients will receive pre-chemotherapy education as per Usual Care at each site. They will also have routine access to the haematology treatment team at each site via: i) scheduled clinic visits, and ii) via hospital switchboards at other times.

#### Intervention group

Patients allocated to the intervention condition will receive standard care as described above in the control group. *In addition* they will also receive the PRISMS intervention.

#### Safety of the intervention

The intervention *is not* designed to replace normal patient contact with the hospital (i.e. Usual Care) but to enhance the current Usual Care. The patient Android application comes equipped with emergency and hospital phone numbers for patient reference and the tablet computer provided can also be used as a phone to contact the hospital when required. Should an error occur in the transmission of patient side-effect data from the patient tablet to the system server/website the software application will advise the patient of the failure of data transmission and, based on alerting algorithms, provide detailed instructions on who and when to call. The server containing the system is monitored daily for performance and any faults addressed by technicians.

### Outcomes

#### Primary hypothesis

Compared to the Usual Care control group, participants receiving the PRISMS intervention will report lower scores item scores for nausea, mucositis, constipation and fatigue of at least 0.4 standard deviations at follow-up (mid-cycle 2 of chemotherapy treatment).

#### Secondary hypotheses

*Specific secondary hypotheses are that:*Participants receiving the PRISMS intervention will report lower scores on item scores for nausea, mucositis, constipation and fatigue compared to the Usual Care control group at follow-up (mid-cycles 3 and 4);Participants receiving the PRISMS intervention will report lower item scores for vomiting and diarrhoea compared to the Usual Care control group at follow-up (mid-cycles 2, 3 and 4);Participants receiving the PRISMS intervention will report lower levels of psychological distress, better quality of life, higher levels of patient activation (ability to self-manage health) and lower levels of cancer information and support needs compared to the Usual Care control group at follow-up (mid-cycles 2, 3 and 4); andThe PRISMS intervention will be cost-effective compared to the Usual Care comparator at follow-up (end of chemotherapy cycles 2, 3, and 4).

Primary and secondary hypotheses for nausea, mucositis, constipation and fatigue differ only in the predicted chemotherapy cycle. This is based on previous qualitative data relating to the PRISMS intervention which suggested that patients find the system to have greatest value in cycles 1 and 2 as well as the issue that not all patients who are originally scheduled to receive 4 cycles of treatment go on to complete all cycles.

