#### Patient inclusion criteria

Patients will be eligible to participate in the trial if they have: a confirmed diagnosis of Hodgkin’s lymphoma, non-Hodgkin’s lymphoma (NHL) or chronic lymphocytic leukaemia (CLL); are scheduled to receive at least 2 cycles of chemotherapy; are aged 18 years and over; and are able to provide informed consent prior to commencing chemotherapy treatment.

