### Data collection

#### Patients

Baseline data will be collected prior to the first chemotherapy treatment cycle. Follow-up data will be collected at 7 time points:At completion of chemotherapy treatment cycle 1 (Follow-up 1)Mid-cycle following of second, third and fourth chemotherapy cycles (Follow-ups 2a, 3a and 4a)At completion of chemotherapy treatment cycles 2, 3 and 4 (Follow-ups 2b, 3b and 4b)

The questionnaires completed at each study time point are summarised in Fig. 1. Data collection has been split across 2 time periods in each treatment cycle so as to allow the capture of side-effect and related outcomes at a point in the cycle where they are likely to be problematic (i.e. Follow-ups 2a, 3a and 4a) as the timeframe for each of the validated outcome measures is within the past week (i.e. Follow-ups 2a, 3a and 4a). Other measures, such as health service usage rely on data from an entire cycle and are, therefore, measured at the conclusion of chemotherapy treatment (CTx) cycles (i.e. Follow-ups 2b, 3b and 4b).

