### Measures

#### Pen-and-paper measures

Demographic Questionnaire (baseline only) will be used to assess basic patient demographic information including: current employment status, occupation, level of education, living arrangements and number/age of children, country of birth, languages spoken) and previous use of technology (including smart phones, computers and the Internet).Rotterdam Symptom Checklist (RSCL) will be used to assess patient symptom burden. The 30-item checklist is appropriate for use in mixed cancer populations including those undergoing chemotherapy, radiotherapy and/or surgery [47]. Participants use a four-point Likert-type scale to rate the extent to which they have been bothered by each symptom during the past week. Item scores can be used to compute three scales including a physical symptom distress level, psychological distress level and activity level impairment. All scales demonstrate acceptable internal consistency (alpha = 0.71–0.90) and good convergent (*r* > 0.58) and discriminative validity [47] and sensitivity to change in a longitudinal setting [48].Functional Assessment of Cancer Treatment – General scale (FACT-G) questionnaire will be used to assess patient health-related quality of life (QOL). The 27-item FACT-G assesses four specific domains including physical, social, emotional and functional well-being [49]. The scaling and unidimensionality of its subscales have been broadly confirmed by both factor and Rasch analysis respectively [50]. FACT-G subscales demonstrate acceptable internal consistency (alpha = 0.72–0.90), good convergent (*r* > 0.51), divergent (*r* < 0.22) and discriminative validity [49] and responsiveness to psychosocial interventions [51].Hospital Anxiety and Depression Scale (HADS) will be used to measure psychological distress [52]. The 14 items of the HADS form a uni-dimensional construct of psychological distress [53]. HADS has demonstrated high internal consistency (alpha = 0.85) in cancer patients [53, 54] and responsiveness to psychosocial interventions [55].EuroQol-5D (EQ-5D) descriptive system and visual analogue scale will be used to assess health utility/QOL. The EQ-5D is a standardised measure [56] of health status developed specifically for economic evaluation. In cancer patients it has acceptable convergent validity (*r* > 0.49), internal consistency (alpha = 0.71), test-retest reliability (kappa = 0.7), discriminative validity and sensitivity to change in a longitudinal setting [57, 58].Patient Activation Measure (PAM; baseline and end of cycle 4 only) will be used to assess patient activation (i.e. ability to self-manage health). The 13 items of the PAM form a unidimensional construct of knowledge, skills and confidence for self-management. It has demonstrated high internal consistency (alpha = 0.90) and excellent discriminative validity based on known group comparisons [59].Cancer Treatment Scale (CaTS; baseline and end of cycle 4 only) will be used to assess cancer treatment-related information and support needs. This 25 item measure forms two subscales: sensory-psychological concerns and procedural concerns. Both subscales demonstrated high internal consistency (alpha > 0.90) and good divergent validity (with the HADS: *r* < 0.26) [60]. Both subscales were sensitive to change in a recent intervention study [13].

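### Patient activation and information/support needs are hypothesised at mid-cycles 2, 3 and 4, but PAM and CaTS are collected only at baseline and end of cycle 4, so only an end-of-cycle-4 comparison is available

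*Protocol article*

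**What the plan says.** Protocol article, Secondary hypotheses: the third hypothesis groups psychological distress, quality of life, patient activation and information/support needs under a single timing. It predicts "higher levels of patient activation (ability to self-manage health) and lower levels of cancer information and support needs" for intervention patients. For the last of these outcomes it reads "cancer information and support needs compared to the Usual Care control group at follow-up (mid-cycles 2, 3 and 4". The same timing governs patient activation.

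Protocol article, Data collection (Patients): the mid-cycle contacts are defined as "Mid-cycle following of second, third and fourth chemotherapy cycles (Follow-ups 2a, 3a and 4a". The ends of cycles 2, 3 and 4 are separate contacts, Follow-ups 2b, 3b and 4b.

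Protocol article, Pen-and-paper measures: each construct has one instrument, and each instrument has a restricted schedule. For activation: "Patient Activation Measure (PAM; baseline and end of cycle 4 only) will be used to assess patient activation". For information and support needs: "Cancer Treatment Scale (CaTS; baseline and end of cycle 4 only) will be used to assess cancer treatment-related information and support needs".

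Protocol article, Patient inclusion criteria: patients qualify if they "are scheduled to receive at least 2 cycles of chemotherapy". The closing paragraph of Secondary hypotheses acknowledges that some patients scheduled for four cycles will not complete them.

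**The concern.** The hypothesis names three follow-up times for two outcomes, and neither instrument is given at any of them. Both outcomes appear in the abstract's list of secondary outcomes. Self-care coaching is a core part of the intervention. PAM is the only measure of self-management that compares the arms, because the PRISMS log data exist only for intervention patients.

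If the text stays as it is, the report must either leave these parts of the hypothesis unanswered or move them to another time point after the event. The one time point that has data also depends on treatment lasting four cycles, which the eligibility criteria do not require. The population behind the comparison therefore needs to be stated.

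**Working it through.** **Step 1. Set the hypothesis beside the collection schedule.** The inputs are the hypothesis timing (Secondary hypotheses), the contact definitions (Data collection) and the instrument schedules (Pen-and-paper measures).

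| Contact | Timing | Named in the hypothesis | PAM and CaTS given |
|---|---|---|---|
| Baseline | before cycle 1 | no | yes |
| Follow-up 1 | end of cycle 1 | no | no |
| 2a | mid-cycle 2 | yes | no |
| 2b | end of cycle 2 | no | no |
| 3a | mid-cycle 3 | yes | no |
| 3b | end of cycle 3 | no | no |
| 4a | mid-cycle 4 | yes | no |
| 4b | end of cycle 4 | no | yes |

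Hypothesised contacts: {2a, 3a, 4a}. Collection contacts: {baseline, 4b}. The intersection is empty, so 0 of 3 named time points have data. The only post-baseline contact with data is 4b, which the hypothesis does not name.

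**Step 2. Check that 4a and 4b are different occasions.** Under Data collection, the mid-cycle questionnaires are mailed and completed at home. The end-of-cycle data are completed with the data manager just before the next chemotherapy appointment. A 4b value therefore cannot stand in for a 4a value.

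**Step 3. Check what remains testable.** Outcome analyses specifies group contrasts at post-baseline time points in a mixed model. For PAM and CaTS that leaves one contrast, at 4b.

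**Step 4. Ask who can contribute at 4b.** Two scheduled cycles are enough for entry, and some patients scheduled for four will not complete them. No contact before 4b supplies a post-baseline PAM or CaTS score. A patient who stops earlier has only a baseline score under the published schedule. The article gives neither the number of patients scheduled for fewer than four cycles nor the number expected to stop, so the loss cannot be calculated from it.

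**Step 5. Confirm that the sample size is untouched.** Inputs from Sample size: effect 0.4 SD, two-sided alpha 0.05, power 80%. The exact t test solves to 99.08 per arm, hence 100 per arm and 200 in total. With 10% attrition, 200 / 0.9 = 222.2, against the stated 222. These figures concern the four primary symptom items and do not depend on PAM or CaTS.

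**The case against.** **It is only loose wording.** One timing phrase covers four outcomes. It conflicts with nothing in the article for distress and quality of life, and it is wrong for the other two. That stands, and it limits the defect to a time label that one sentence can correct. The label still cannot be read as end of cycle: the next hypothesis in the same section uses end-of-cycle timing for cost-effectiveness, and Data collection explains why the two kinds of contact were separated.

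**Fig. 1 or a SAP may settle it.** The figure that summarises questionnaires by time point is not shown. The schedule for both instruments is nevertheless explicit in the text. A SAP can choose a contrast but cannot supply scores that were not collected.

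**Baseline and end of intervention is a sound schedule for these constructs.** This stands. The measurement plan is defensible; it is the hypothesis that does not match it.

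**The mixed model uses all available data, and a drop-out comparison is planned.** This stands in part. With no assessment between baseline and 4b, a missing 4b score is informed only by the baseline score and rests on a missing-at-random assumption.

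A reader might also infer three stronger points that the article does not support:
- That the two constructs cannot be compared at all. They can, at 4b.
- That there is a quantifiable loss of power against 200 patients and 0.40 SD. That target was set for the primary symptom items. No power is claimed for PAM or CaTS, and no rate of stopping before cycle 4 is given.
- That moving both instruments to Follow-up 2b would reach every eligible patient. End-of-cycle data are collected just before the appointments for cycles 2 to 5, which pairs 2b with cycle 3. The article does not say how 2b is obtained from a patient with no third cycle.

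**Conclusion.** The contradiction is real and exact. The activation and information/support-needs parts of the third secondary hypothesis have data at none of their three stated time points. Both can be compared between arms at the end of cycle 4, so the untestability applies to the hypothesis as timed and not to the constructs themselves. Distress, quality of life, the primary analysis and the sample size are unaffected.

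The 4b comparison will lack patients who stop before the end of cycle 4. This rests on the published schedule and assumes that no arrangement outside the article collects the instruments from early stoppers. The size of that loss is unknown. The matter is limited to secondary outcomes, but it should be corrected because it is cheap to do and avoids retiming a hypothesis after the data are seen.

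**What to change.** 1. Split the third secondary hypothesis. Keep the mid-cycle timing for distress and quality of life, and state the PAM and CaTS hypothesis at the end of cycle 4 (Follow-up 4b). This is a text change with no added data collection.
2. Make the 4b comparison adjusted for the baseline PAM or CaTS score. That score is already collected, and baseline-adjusted analysis is already mentioned under Outcome analyses.
3. Describe the result as resting on patients who reach cycle 4, and report by arm how many contribute a 4b score.
4. Optional supplement: for patients not yet past cycle 2, also give PAM and CaTS around the end of cycle 2, by mail where there is no cycle 3 appointment. Mailing is already used for the mid-cycle questionnaires. The cost is 13 + 25 = 38 extra items per patient and an amendment at both ethics committees. The trial is already recruiting, so coverage of enrolled patients would be incomplete. The result should therefore support the 4b comparison and not replace it.
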